**SUPPORTING INFORMATION: Trial Protocol**

# Effects of rhGH and Pioglitazone in Viscerally Obese Adults with IGT

A. **ABSTRACT**

People with impaired glucose tolerance (IGT) who lose visceral fat also tend to lower their risk of developing diabetes. This benefit occurs because visceral fat reduction improves insulin sensitivity and reduces postprandial glucose levels. Thiazolidinediones (TZDs) and growth hormone (rhGH) taken independently foran *extended period of time* can reduce visceral fat and improve endogenous insulin sensitivity. However, in the *short-term* (ie: first 6 weeks of treatment) rhGH may increase insulin resistance. In contrast, a TZD added to rhGH prevents short-term rhGH-induced insulin resistance in experimental animals, suggesting a possible therapeutic benefit with this drug combination in humans. In addition, like rhGH, TZDs mediate some of their insulin sensitizing effects by reducing visceral fat depots. It is therefore possible that the addition of a TZD with standard growth hormone therapy will optimize the short-term and long-term improvements in body composition, insulin sensitivity and glucose metabolism in humans.

The specific aims of this study are as follows: (1) to assess the effects of TZDs with and withoutrhGH on visceral fat content, insulin sensitivity and postprandial glucose levels in viscerally obese subjects with IGT; *and* (2)to compare the effects of TZDs *plus* rhGH with rhGH alone on short-term glucose metabolism. Sixty adult men and women between the ages of 40 and 75 will be recruited to participate and will receive a TZD and rhGH in a double-blind manner. During weeks 0-4, a “run-in” period, subjects will receive a TZD or oral placebo. During weeks 5-40, a TZD or oral placebo will be co-administered with rhGH or a subcutaneous placebo in a 2 X 2 study design. Short-term glucose metabolism will be monitored using fasting glucose levels. Changes in visceral fat content will be quantified using abdominal CT scanning and anthropometric measurements. At baseline and after 9 months of combination drug or placebo treatment, serum postprandial glucose levels will be measured using a standard oral glucose tolerance test, and endogenous insulin sensitivity will be measured using a hyperinsulinemic euglycemic clamp.

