It is expected that the combined use of a TZD and rhGH will be more efficacious in reducing visceral fat quantity and improving insulin sensitivity in viscerally obese adults with IGT compared with the use of either drug alone. The potential long-term benefit of this finding is a reduction in the incidence of type 2 diabetes in populations at high risk of developing diabetes, such as individuals with visceral obesity and IGT.

B. **HYPOTHESES AND SPECIFIC AIMS TO TEST HYPOTHESES**

***Hypothesis #1:*** Subjects who receive rhGH and pioglitazone for 9 months will achieve greater visceral fat reduction, improved insulin sensitivity and lower postprandial glucose levels compared with subjects who receive placebo.

***Specific aim to test hypothesis #1:*** We will assess the effects pioglitazone with and without prolonged rhGH administration on visceral fat change and determine whether change in visceral fat quantity is associated with changes in endogenous insulin sensitivity and postprandial serum glucose levels.

***Hypothesis #2:***Subjects who receive pioglitazone *and* rhGH will demonstrate less transient worsening in glycemic control during the first 6 weeks of treatment compared with subjects who receive rhGH alone.

***Specific aim to test hypothesis #2:***We will compare the effects of a TZD *plus* rhGH with rhGH alone on short-term glucose metabolism. In doing so, we will also determine whether the co-administration of a TZD can effectively counteract the expected transient rise in insulin resistance associated with rhGH and help to maintain better short-term postprandial glucose control compared with rhGH alone.

C. **BACKGROUND**

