Visceral fat loss reduces postprandial glucose levels in IGT patients (13-19). Fujioka et. al showed that weight loss - and visceral fat reduction in particular - results in a significant reduction in postprandial glucose levels in viscerally obese women with IGT (20). Eriksson et. al also prospectively showed that IGT subjects achieved lower postprandial glucose levels after weight loss, and that this reduced the overall risk of developing type 2 diabetes (21). In addition, recently published data from the Diabetes Prevention Program (DPP) study indicate that a 5-7 % weight loss in IGT subjects reduces the risk of developing type 2 diabetes by 58% (22).

***GH, visceral fat reduction and enhanced insulin sensitivity:*** Growth hormone (GH), a glycopeptide hormone produced in the anterior pituitary, helps to maintain normal body composition and reduce visceral fat in adults (23). It also appears to have various effects on glucose, lipid and bone metabolism.

Viscerally obese adults have below normal integrated GH concentrations as measured by an ultrasensitive chemiluminescence assay (24). The association between visceral obesity and an apparent “underproduction” of GH has recently prompted several investigators to study the effects of rhGH on body composition and metabolism in viscerally obese adults. In a recent study, Johannsson et. al investigated the effects of rhGH in insulin resistant, viscerally obese men with normal glucose tolerance (25). As expected, subjects receiving rhGH lost a substantial amount of visceral fat – almost 18%. In addition, while overall glucose levels did not change during the study, an interesting paradoxical effect on short-term versus long-term insulin sensitivity occurred in rhGH-treated subjects. RhGH-treated subjects developed a transient *decrease* in insulin sensitivity as expected during the first 6 weeks of therapy. However, after 9 months of rhGH treatment, the glucose disposal rate (GDR), a measure of tissue insulin sensitivity*, increased* by 1.2 +/- 0.7 mg/kg per minute compared to baseline (*P* < 0.05), indicating that insulin sensitivity increases – rather than decreases - with long-term rhGH administration.

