    How does GH cause a *transient* insulin resistance? GH exerts a direct antagonistic effect on the insulin signaling pathway in muscle cells. GH inhibits the insulin-induced activation of so-called insulin receptor substrate (IRS) proteins, and these “inactivated” proteins cannot trigger the usual cascade of events that ultimately lead to glucose uptake into tissues. Despite the antagonistic effects of GH on insulin, euglycemia is usually maintained because the pancreatic beta-cell increases insulin output in order to overcome tissue insulin resistance.

    What causes the subsequent increase in insulin sensitivity that occurs with prolonged rhGH administration? Visceral fat loss. This happens as follows: visceral fat, a vast depot of lipid-rich substances, releases large quantities of free fatty acids (or FFAs) into the circulation. FFAs cause insulin resistance by blocking the insulin-induced expression and cell surface translocation of proteins that mediate glucose transport into cells, called glucose transporter (or GLUT) proteins. A selective reduction in visceral fat, as occurs with prolonged rhGH administration, leads to diminished free fatty acid (FFA) flux, and this allows insulin-GLUT-mediated glucose disposal to occur. While rhGH directly antagonizes insulin in skeletal muscle, rhGH-induced visceral fat disappearance leads to enhanced insulin action in *multiple* tissue compartments, including adipocytes, skeletal tissue, hepatocytes, and other cells throughout the body. As a result, the indirect insulin “sensitizing” effects of visceral fat reduction with prolonged rhGH administration outweigh its direct insulin resistant effects, and the net result is a rise in endogenous insulin sensitivity (25).

    Visceral fat reduction and the insulin sensitive state that follows help to lower postprandial glucose levels in individuals with IGT. Postprandial glucose reduction occurs in this setting because insulin, now free from the antagonizing effects of FFAs, is able to turn off gluconeogenesis, or glucose production, in the liver and stimulate the uptake and clearance of glucose into muscle and other tissues. It is possible that similar improvements in glucose metabolism will occur in viscerally obese IGT patients who receive rhGH. However, this is theoretical. Prospective studies are needed to determine the effects of prolonged rhGH on glucose metabolism in this population.

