#### STUDY ENDPOINTS

**Oral glucose tolerance test:** As per the technique described under screening, a 75 gram OGTT will be repeated at week 43, approximately 3 weeks after discontinuation of all study medications (washout period). In addition, the glucose area under the curve, or AUC, will be measured using the trapezoid method. Based on previously published data, we expect that rhGH administration will cause at least a 10% reduction in both postprandial glucose (2 hours post OGTT) and glucose area-under-the-curve compared to baseline values.

**CT of the abdomen:** A non-contrast CT of the abdomen to quantify visceral adiposity will be obtained at the baseline visit and again at week 40. This imaging technique is among the most reliable for measuring visceral fat (32). Scans will be

obtained at 5 levels: spleen/liver, L3-4 lumbar disc, L4-5 lumbar disc, lower edge of pubic symphysis, and upper thigh (with reference to edge of lower symphysis). The area of the visceral and subcutaneous abdominal fat compartments at the

5 levels will be measured and recorded in centimeters squared. Abdominal visceral volume will then be calculated (in liters) using the visceral tissue areas of the 5 scans and the measured distances between them. The same CT scanner will be used at the start and completion of the study, and the same radiologist at VA Palo Alto will analyze all scans.

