**Insulin Sensitivity Test (IST):** Endogenous insulin sensitivity will be measured using a 3-hr insulin sensitivity test (33,34). This test will be performed at baseline and again at week 43 (which follows a 3-week washout period for study medications). An intravenous catheter will be placed into each antecubital vein. One catheter will be used for blood draws for glucose measurements and the catheter in the contralateral arm will be used for infusion of octreotide, insulin and 20% dextrose. The 3 infused substances will be administered simultaneously. Octreotide acetate will be used to suppress endogenous secretion of insulin and will be infused at 0.27 µg/m2 per minute. Insulin will be infused at 32 mU/m2·min and glucose will be infused at 267 mg/m2 per minute. Serum glucose will be measured every 30 minutes for the first 150 minutes and then every 10 minutes during the last half hour of the test. The last 4 serum glucose measurements will averaged and recorded in mg/dl and will constitute the subject’s steady state plasma glucose (or SSPG). The SSPG provides a direct measure of insulin-mediated glucose uptake and will be used to describe each subject’s insulin sensitivity (33,34).

**Anthropometrics:** BMI, waist circumference and WHR will be measured at baseline and at weeks 8, 16, 32 and 40.

**IGF-1 levels:** Serum insulin like growth factor 1, or IGF 1, is a marker of GH status in the body. IGF 1 levels will be drawn at baseline and again at weeks 8, 16 and 32 and will be used along with clinical symptoms to assess rhGH dose adequacy. IGF 1 values greater than 2 standard deviations above the adult reference mean will result in a 50% rhGH dose reduction.

**Liver function tests, fasting glucose, hemoglobin (Hgb) A1C:** LFTs will be obtained at baseline and again at weeks 8, 16, 24, 32 and 40. Fasting glucose levels will be measured at baseline and at weeks 4, 8, 12, 16, 20, 24, 32 and 40. A HgbA1C will be used to measure each subject’s long-term glucose control and will be obtained at baseline and at weeks 8, 16 and 40.

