Serum glucose levels may transiently rise with rhGH due to its insulin antagonizing effects. It is expected that subjects in the combined pioglitazone/rhGH treatment group will be “protected” from this effect, whereas rhGH subjects *not* co-treated with a TZD may be susceptible. However, previous studies have shown that this susceptibility is reduced when moderate, rather than excessive, doses of rhGH are used (35). Marcus et. al showed that subjects with impaired glucose tolerance treated for 1 week with rhGH doses comparable to ours maintained similar glucose concentrations before and after treatment (37). In addition, Johannsson et. al showed that glycemic deterioration did not occur when rhGH doses similar to ours were used in people with underlying insulin resistance (25).

     The following measurements obtained on at least two separate occasions will be considered abnormal: (a) IGF-1 level greater than 2 standard deviations above the adult reference mean; OR (b) fasting glucose >126 mg/dl or random glucose > 200 mg/dl *plus* symptoms (ie: polyuria, polydipsia, ketosis) according to the revised ADA definition of diabetes mellitus. These abnormalities will result in the changes/interventions listed in *APPENDIX A* (please see *Page 13)*. *In order to maintain the study blind, a third-party investigator will be responsible for all drug dose adjustments during this study*.

The development of mild-to-moderate peripheral edema or symptoms indicative of rhGH-induced fluid retention (such as carpal tunnel syndrome, arthralgias, paresthesias) will also result in rhGH and/or TZD dose adjustments according to the algorithm in *APPENDIX B* (please see *Page 14*). In addition, the development of very severe or clinically life-threatening edema (ie: frank pulmonary edema, congestive heart failure) at any time during the study will result in prompt subject discontinuation.

*Thiazolidinediones (TZDs)*: TZDs can elevate liver function tests such as SGOT or SGPT. However, this is rarely clinically significant. Subjects will be discontinued from the study if LFTs are more than 2.5 times the upper normal range. In uncontrolled diabetics, weight gain may occur with TZDs as glucose levels fall. When serum glucose falls, glycosuria or excess glucose spillage in the urine ceases, and glucose is taken up into tissues. This often results in weight gain. Unlike uncontrolled diabetics, significant glycosuria does not usually

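### Aim 2 says it will determine early insulin resistance and postprandial glucose on rhGH, but neither is measured in that period; only its fasting-glucose part can be tested.

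*Protocol*

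**What the plan says.** Section B of the Protocol frames Hypothesis 2 as less transient worsening of glycemic control over the first 6 weeks of treatment with pioglitazone plus rhGH than with rhGH alone. The first sentence of the matching aim is a comparison of short-term glucose metabolism. The second sentence adds two further outcomes: whether a TZD can "effectively counteract the expected transient rise in insulin resistance associated with rhGH" and whether it can "help to maintain better short-term postprandial glucose control compared with rhGH alone".

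The Abstract names the short-term measure: "Short-term glucose metabolism will be monitored using fasting glucose levels".

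The Study Endpoints section sets the other tests. For postprandial glucose, "a 75 gram OGTT will be repeated at week 43", about 3 weeks after all study medication has stopped; the first OGTT is the screening one. For the insulin sensitivity test (IST), "This test will be performed at baseline and again at week 43", after the same washout. Fasting glucose is taken at baseline and weeks 4, 8, 12, 16, 20, 24, 32 and 40. HbA1c is taken at baseline and weeks 8, 16 and 40, and is described as a measure of long-term control. Fasting insulin is not listed.

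On how glucose behaves under rhGH, the Background says of the cited 9-month study that insulin sensitivity fell in the first 6 weeks "while overall glucose levels did not change during the study". It explains that "euglycemia is usually maintained because the pancreatic beta-cell increases insulin output in order to overcome tissue insulin resistance". The section on drug side effects reports that "glycemic deterioration did not occur when rhGH doses similar to ours were used in people with underlying insulin resistance", but the same paragraph opens by allowing that serum glucose may rise transiently on rhGH.

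**The concern.** The two outcomes in the second sentence of Aim 2 need a postprandial test and a measure of insulin resistance during early rhGH exposure. If neither is taken then, no analysis can supply them, and a statistical analysis plan cannot create unscheduled measurements.

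What is left for that period is fasting glucose, and the protocol's own account of rhGH partly uncouples it from insulin resistance. If extra insulin output compensates, fasting glucose may change little while resistance rises. A null fasting-glucose comparison could then be misread as showing no rhGH-induced resistance, or no protection by pioglitazone. A positive comparison would still not support a statement about postprandial glucose or insulin resistance. The Significance section builds on this aim: it devotes a subsection to preventing rhGH-induced insulin resistance in the first 6 weeks and names five patient populations as future candidates for the combination.

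**Working it through.** **Step 1: the window.** Section D starts rhGH at week 5. Six weeks from there is about weeks 5 to 10.

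**Step 2: scheduled measurements against the window** (times from Study Endpoints and the OGTT screening paragraph).

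| Measure | Scheduled times | In weeks 5–10 | In weeks 5–40 (on rhGH) |
|---|---|---|---|
| OGTT | screening, 43 | 0 | 0 |
| IST | baseline, 43 | 0 | 0 |
| Fasting insulin | none | 0 | 0 |
| Fasting glucose | baseline, 4, 8, 12, 16, 20, 24, 32, 40 | 1 (week 8) | 7 |
| HbA1c | baseline, 8, 16, 40 | 1 (week 8) | 3 |

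The Abstract places the postprandial and insulin-sensitivity tests at baseline and after 9 months, which is no earlier.

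**Step 3: the other reading of the window.** If the 6 weeks are counted from week 0, the only on-treatment glycemic value inside them is the week 4 fasting glucose, taken before any rhGH. The gap is then wider.

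**Step 4: outcome by outcome.**
- Short-term glucose metabolism (Hypothesis 2 and the first sentence of Aim 2): testable on fasting glucose, with one in-window sample.
- Transient insulin resistance: not measured in the window.
- Short-term postprandial glucose: not measured in the window.

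**Step 5: illustration of what fasting glucose could detect.** The protocol gives no power figure for Aim 2, so there is none to reproduce. Take group 4 against group 2 with n = 15 each, a two-sided 5% test, 80% power, and a t test at a single time point.
- Normal approximation: d = (1.960 + 0.842) × √(2/15) = 1.02 SD. By the exact noncentral t distribution, d = 1.06 SD.
- The protocol gives no SD for fasting glucose. At assumed SDs of 8, 10, 12 and 15 mg/dl, 1.06 × SD = 8.5, 10.6, 12.7 and 15.9 mg/dl.
- Analysed as change from baseline with correlation ρ, the factor is √(2(1 − ρ)). At assumed ρ = 0.6, 1.06 × 0.894 = 0.95 SD; at ρ = 0.8, 1.06 × 0.632 = 0.67 SD.

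Step 5 only gives scale. The conclusion rests on Steps 1 to 4.

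**The case against.** The best counter-argument is that the aim is narrower than its second sentence. Hypothesis 2 speaks of glycemic control, the first sentence of Aim 2 of short-term glucose metabolism, and the Abstract states the aim without insulin resistance or postprandial glucose and names fasting glucose as its measure. This stands. A reader might infer that Aim 2 as a whole cannot be answered; the documents do not support that. Only the added second sentence lacks its measurements.

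A reader might also infer that the protocol predicts flat fasting glucose on rhGH, which would make the comparison empty. The protocol does not go that far. The side-effects section says glucose may rise transiently and that rhGH subjects without a TZD may be susceptible. The unchanged result in the 9-month study concerns overall glucose, not specified as fasting, in men with normal glucose tolerance. The cited evidence in impaired glucose tolerance covers 1 week. The Background describes that condition as one in which insulin release fails to overcome resistance, and reports abnormal glucose control in rats given rhGH alone. Compensation is therefore described as usual, not certain.

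It can further be said that if glucose does not rise on rhGH alone, a null result is the correct answer to Hypothesis 2. That is right; the harm arises only if the null is read as evidence about insulin resistance, and the second sentence of Aim 2 invites that reading.

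Finally, HbA1c at week 8 is a second in-window measurement. It is labelled long-term and measures neither missing outcome.

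**Conclusion.** The point holds for the second sentence of Aim 2. Two outcomes that the trial says it will determine have no measurement in the first 6 weeks of rhGH, and no OGTT or IST is scheduled at any time on rhGH. This follows from the schedule alone, under either way of counting the 6 weeks.

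That fasting glucose is a weak stand-in for insulin resistance rests on the protocol's own description of compensation by the beta-cell, qualified by its allowance for a transient rise. The 1.06 SD figure illustrates a single-time-point t test with an assumed SD. The protocol plans repeated-measures ANOVA, and an analysis using baseline could detect less. A reader might go on to infer that a significant Aim 2 result would occur only at the 5% false-positive rate. That needs full compensation and no effect of pioglitazone on fasting glucose. The protocol states neither, and groups 3 and 4 take pioglitazone from week 0.

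The two primary efficacy endpoints behind the sample size, visceral fat and insulin sensitivity, are not affected. The matter should still be settled before enrolment, because early on-drug measurements cannot be recovered later unless suitable samples were stored.

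**What to change.** Choose one of two changes.

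1. **Limit the aim.** Restrict Aim 2 and the conclusions drawn from it to fasting glucose. Delete the insulin-resistance and postprandial claims. State that a null fasting-glucose result does not show absence of rhGH-induced insulin resistance. Bring the Significance subsection on the first 6 weeks into line. This costs wording only.

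2. **Keep the insulin-resistance part and measure it.** Assay insulin in the fasting blood already drawn at baseline, week 4 (the reference before rhGH), week 8 (in the window) and weeks 12 and 16 (later course). Add a fasting insulin-glucose index, such as log HOMA-IR, as the insulin-resistance endpoint. Fasting glucose remains the measure for Hypothesis 2. The cost is 60 subjects × 5 draws = 300 assays, with no new visit. The index is a surrogate, and only week 8 falls in the first 6 weeks of rhGH. The postprandial claim must still be deleted, because a fasting index says nothing about it.

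Under either change, state that the 6 weeks are counted from the start of rhGH at week 5, so that the week 8 sample is identified as the in-window measurement.

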#### SCREENING TESTS FOR SUBJECT SELECTION

**Physical exam:** Screening will include a complete medical history and physical examination. In addition, vital signs and blood pressure measurements will be performed.

**Anthropometric measurements:** Body mass index (in kg / height in meters squared), waist circumference (in inches), hip circumference (in inches), and waist-to-hip ratio (WHR) will be measured. The criteria for inclusion in this study is a BMI > 27 *plus* EITHER waist circumference > 40 inches in men or > 38 inches in women OR WHR >0.9 in men or >0.8 in women. These measurements are associated with both increased visceral adiposity and greater cardiovascular risk (2,30,31).

**Laboratory studies and ECG:** Liver function tests (LFTs) will be obtained in all subjects, and male subjects will have prostate specific antigen (or PSA) levels measured. Women of child-bearing potential will have a urine pregnancy test to exclude pregnancy. All blood and urine studies will be done at the VA Medical Center, Palo Alto, CA, and results will be compared to normal VA laboratory reference values. A supine electrocardiogram (ECG) will also be obtained.

**Oral Glucose Tolerance Test:** Once subjects have passed this background screening, they will be given an oral glucose tolerance test (OGTT). After an overnight fast, subjects will come to the VA and drink a 75 gm glucose beverage. Serum glucose levels will be measured at 0 min (fasting), 30 min, 60 min, 120 min and 180 min after glucose ingestion.

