**Subjects:** Men and women between the ages of 40 and 75 with visceral obesity and IGT will be recruited to participate. This age group has a higher prevalence of both visceral obesity and IGT.

Specific inclusion criteria are as follows: (a) adults between the ages of 40 and 75; (b) fasting glucose less than 120 mg/dl PLUS 2 hour postprandial glucose level during 75 gram OGTT between 140 – 200 mg/dl; (c) BMI > 27; and (d) increased waist circumference and/or increased waist-to-hip ratio (*see anthropometric measurements* below).

Subjects will be free of major medical illnesses such as uncontrolled hypertension, congestive heart failure or active malignancies. Women of child-bearing potential who are or plan to become pregnant or will breastfeed an infant will be excluded. Subjects taking corticosteroids or other medications that can significantly alter glucose metabolism will also be excluded. Groups will be matched on gender, BMI, estrogen status, and 2-hr glucose level (during screening OGTT). A third party investigator will be responsible for all randomization and coding of medications and placebo.

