#### EXPERIMENTAL DESIGN

After screening, 60 men and women who meet the criteria for study inclusion will be randomly assigned into 4 groups, with each group containing 15 subjects (n=15). The treatment period will start at week 0 and continue for 40 weeks total.  **During** **weeks 0-4**, *groups 1 and 2* will receive an oral placebo and *groups 3 and 4* will receive pioglitazone orally every day. **During weeks 5-40**, *group 1* will continue the oral placebo and self-inject a SQ placebo and *group 2* will continue the oral placebo and self-inject rhGH. Also **during weeks 5-40**, *group 3* will continue pioglitazone and self-inject a SQ placebo and *group 4* will continue pioglitazone and self-inject rhGH.

*Group 1* (n=15): Oral placebo plus SQ placebo.

*Group 2* (n=15): Oral placebo plus rhGH.

*Group 3* (n=15): Pioglitazone plus SQ placebo.

*Group 4* (n=15): Pioglitazone plus rhGH.

Sample size was determined using data from Johannsson et. al, 1997 in which a dose of rhGH comparable to ours was used to achieve a 17.9 +/- 3.5 percent change in visceral fat volume and an increase in insulin sensitivity of 1.2 +/- 0.6 mg/dl  hr over time (24). Using this information, we have powered our study based on 2 primary efficacy endpoints as follows: (a) 12 subjects (n=12) are needed *per group* in order to have an 80% chance of detecting a change in visceral fat volume of at least 17.9 percent, and (b) 15 subjects (n=15) are needed *per group* in order to have an 80% chance of detecting a change in insulin sensitivity of at least 17.6 percent. Therefore, our sample size for this study will be 15.

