**Study drugs:** The TZD that will be used is *pioglitazone hydrochloride*. Subjects in groups 3 and 4 will begin pioglitazone 15 mg orally every day for 8 weeks total. During weeks 9-12, subjects who have tolerated 15 mg pioglitazone daily will be increased to 30 mg/day and will remain at this dose for the duration of the study. However, the pioglitazone dose may be decreased or, in rare circumstances, increased if side effects such as peripheral edema or diabetes develop (please see *Pages 13 and 14* for TZD dose adjustments). Pioglitazone has been prospectively shown to reduce visceral fat content and improve insulin sensitivity in insulin resistant people. It is begun 4 weeks prior to rhGH in order to allow sufficient time for its insulin sensitizing effect to occur. RhGH-treated subjects will begin self-injecting rhGH 8 mcg/kg SQ every day at week 5 and will continue to do so for the duration of the study, unless side effects develop (please see *Pages 13 and 14* for rhGH dose adjustments). The total rhGH treatment period will be 9 months. Previous studies have indicated that this dosage and duration of treatment are generally well tolerated and effective in significantly reducing visceral fat.

**Diet, exercise and activity:** Subjects will adhere to their usual daily dietary consumption and exercise routine for the duration of the study. They will be asked to report any significant changes in dietary intake or physical activity.

**Physical exam:** A complete physical exam will be performed at baseline (week ­- 4 to 0) and again at weeks 4, 8, 12, 16, 20, 24, 32, 40 and 43. In addition, supine systolic and diastolic blood pressure will be measured in mmHg using a manual sphygmomanometer.

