occur in IGT patients. Therefore, TZD-induced weight gain is expected to be minimal in our study. In addition, TZDs can infrequently cause peripheral edema that is usually mild. *Table 3* summarizes the side effects that may occur with TZDs, according to Foyt, et. al, 2000 (38,39,40).

Table 3 (Adapted from Thiazolidinediones. Diabetes Mellitus: a Fundamental and Clinical Text. Lippincott Williams and Wilkins:788-797, 2000):

1. LFT increase  0.2% incidence of ALT > 3X upper limit of normal (placebo

= 0.2%)

2. Anemia  Hemoglobin decreases 0.64 g/dL; hematocrit decreases 2%

3. Edema  4.8% vs. placebo = 1.3%

4. Cardiac function  No change in LV mass or function; no data on stroke volume

5. Weight gain  1.2 kg with 4 mg dose; 3.5 kg with 8 mg dose; 2.3 kg with 8

(mean) mg dose + metformin; not reported for 4 mg dose + sulfonylurea

Subjects will be weighed at each P.E. visit and examined very carefully for peripheral edema. The development of mild-to-moderate peripheral edema during the treatment period will result in pioglitazone and/or rhGH dose adjustments according to the algorithm in *APPENDIX A* (please see pages 13 and 14). In addition, the development of very severe or clinically life-threatening edema (ie: frank pulmonary edema, congestive heart failure) at any time during the study will result in prompt subject discontinuation.

    Subjects will be instructed to report side effects that develop during the study by calling the Clinical Studies Unit or by appearing for an unscheduled evaluation.

2. **Alternative Approaches**

Estrogen-treated subjects: Oral estrogen can sometimes antagonize the action of GH at the GH receptor level. This results in lower IGF 1 levels despite normal or even high levels of GH (41,42,43). Adult GHD women taking oral estrogen can require twice as much rhGH as adult GHD men because IGF 1 levels may be 50% lower in the estrogen-treated women.

      An alternative approach is to use a higher rhGH dose in estrogen-treated subjects. However, subjects in this study are non-GHD adults, and higher doses of rhGH may produce unacceptable side effects and abnormally high IGF 1 levels. Therefore, subjects will receive the same starting dose and groups will be matched for menopausal status and estrogen use.

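### The protocol body schedules a urine pregnancy test only at screening, with none during 40 weeks of study drug or before the week-40 research CT

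*Protocol*

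**What the plan says.** Eligibility (Protocol, section D, Subjects): "Women of child-bearing potential who are or plan to become pregnant or will breastfeed an infant will be excluded". The age range is 40 to 75 and both sexes are recruited, so a woman of child-bearing potential who is neither pregnant, planning pregnancy nor going to breastfeed may enter.

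Testing (Protocol, "SCREENING TESTS FOR SUBJECT SELECTION", Laboratory studies and ECG): "Women of child-bearing potential will have a urine pregnancy test to exclude pregnancy". No repeat is given there.

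Exposure (Protocol, Experimental Design): "The treatment period will start at week 0 and continue for 40 weeks total". Physical examinations are at baseline "and again at weeks 4, 8, 12, 16, 20, 24, 32, 40 and 43".

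Imaging (Protocol, Study Endpoints, abdominal CT paragraph): "A non-contrast CT of the abdomen to quantify visceral adiposity will be obtained at the baseline visit and again at week 40". The scans are "obtained at 5 levels: spleen/liver, L3-4 lumbar disc, L4-5 lumbar disc, lower edge of pubic symphysis, and upper thigh".

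Reporting (Protocol, Drug side effects): "Subjects will be instructed to report side effects that develop during the study by calling the Clinical Studies Unit", or by coming in for an unscheduled evaluation.

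**The concern.** Excluding women who plan a pregnancy shows that the sponsor wants none to occur on treatment. The scheduled procedures check for pregnancy only before entry. After that, a pregnancy would come to light through symptoms, examination or the woman's own report, and none of these is a test for early pregnancy. Two exposures are at stake: continued pioglitazone, rhGH or both, and a CT with a pelvic level that serves a research measurement and not the woman's care.

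This concerns participant safety. It does not touch the estimates, the power or the analysis. Nor is it something a statistical analysis plan would be expected to supply.

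**Working it through.** The protocol gives no figure on this point to reproduce. The check is a comparison of sections, followed by a count of tests and intervals.

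**Step 1. Could the situation arise?** Yes. The lower age limit is 40, the eligibility rule leaves room for women of child-bearing potential, and the Alternative Approaches section (estrogen-treated subjects) balances the groups on menopausal status. Premenopausal women were therefore foreseen. Their number is not given.

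**Step 2. What does the body schedule on study?** The weeks below come from the screening section and from Study Endpoints.

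| Test | Screening or baseline | On-study weeks named |
|---|---|---|
| Liver function tests | yes | 8, 16, 24, 32, 40 |
| Fasting glucose | yes | 4, 8, 12, 16, 20, 24, 32, 40 |
| IGF-1 | yes | 8, 16, 32 |
| HbA1c | yes | 8, 16, 40 |
| Urine pregnancy test | yes (screening) | none |

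Liver tests and the pregnancy test stand in the same screening paragraph. The first is carried into treatment with named weeks; the second is not. The visit table (Tentative Sequence for Investigation) is not used as evidence, because it is headed tentative and its columns are broken in the text at hand.

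**Step 3. Count.** Pregnancy tests scheduled: 1 at screening, 0 during weeks 0 to 40, 0 before the week-40 CT.

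**Step 4. Interval from the listed test to the CT.** Screening precedes week 0, so the interval is at least 40 − 0 = 40 weeks. If screening falls in the week −4 to 0 baseline window (an assumption), it is at most 40 − (−4) = 44 weeks. This is the distance between two procedures. It is not an estimate of how long a pregnancy would go unnoticed.

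**Step 5. Effect of repeating the test.** Tests before the first dose (week 0), at weeks 8, 16, 24 and 32, and before the CT at week 40:

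- number of tests: 1 + 4 + 1 = 6
- intervals: 8, 8, 8, 8 and 8 weeks, so the longest is 8

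For comparison, testing at week 0 and at every visit (4, 8, 12, 16, 20, 24, 32, 40) takes 9 tests. The intervals are six of 4 weeks and two of 8, so the longest is again 8. The lighter schedule gives the same longest interval with three fewer tests.

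**The case against.** **Nothing is contradicted.** The eligibility rule and the screening test agree, and the test is right for entry. Some other items, such as PSA and the ECG, are also listed only at screening. This stands: the sentence on testing contains no error. But the aim behind the exclusion extends into treatment and the procedures do not.

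**It may be on pages not shown.** Consent pages were removed, and not every appendix cited is present. This stands in part. A reader might infer that the trial has no contraception advice and no rule for a pregnancy on study; the documents do not support that, because such text could well be on the consent pages. The narrower point holds because the body is where the protocol places its on-study test weeks. The appendices are described there as dose-adjustment rules, which is not where a testing schedule would be looked for.

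**Study Endpoints is not a safety schedule.** Silence there would be weak evidence if the section were purely about efficacy. It also sets out liver tests and IGF-1 with their weeks, so it serves as the on-study laboratory schedule as well.

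**Other safeguards exist.** There are eight physical examinations from week 4 to week 40, with weighing, and participants are told to report side effects. A reader might infer that a pregnancy would otherwise stay hidden until treatment ends. The documents do not support that: examination or symptoms would usually reveal it sooner. What remains is the early period, which neither safeguard tests.

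**Harm is not quantified.** The protocol gives no fetal risk for either drug and no CT dose. This stands, and no size of harm is claimed here. The case rests on the protocol's own wish to exclude pregnancy and on the scan having no clinical purpose for the woman.

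**Conclusion.** The point holds as a minor, inexpensive safety improvement. The body schedules one pregnancy test, before entry, and none during 40 weeks of study drug or before a research CT with a pelvic level. The only listed test precedes that CT by at least 40 weeks, or by 40 to 44 weeks if screening falls in the baseline window.

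Confidence is medium, because unseen pages might already add tests. The number of women of child-bearing potential among the 60 participants is not stated and is probably small at ages 40 to 75, so no expected number of pregnancies is given. A reader might infer that one particular testing frequency is required. The documents do not fix one: the tests before first dose and before the CT matter most, and the spacing between them is a choice.

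**What to change.** For women of child-bearing potential, add to the protocol body and the visit schedule:

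1. a negative urine pregnancy test before the first dose of study drug;
2. a repeat at existing on-treatment visits, for example with the liver tests at weeks 8, 16, 24 and 32;
3. a negative test on the day of the week-40 CT, before scanning;
4. unless pages not shown already say so, a sentence that a positive test stops oral and injected study drug and cancels the CT.

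If the consent pages or an appendix already require this, a cross-reference from the body is enough.

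Cost: six urine strips per woman, one schedule row and one or two sentences. The ceiling is 6 × 60 = 360 strips if every participant were such a woman; the real number is probably far lower. Five of the six tests fall at visits already planned. The test before the first dose needs a separate moment only if the baseline visit is not at the start of dosing.
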